## Abstract

Purpose: The primary aim of this study is to determine the influence of an intervention in women based on a free mobile application (LactApp^®^, Barcelona, Spain) in maintaining breastfeeding (BF) up to 6 months postpartum. The secondary aim is to assess the effect of health literacy (HL) on breastfeeding duration. Methods: A multicenter, randomized controlled clinical trial of parallel groups will be carried out. Women will be randomly assigned to each of the parallel groups. In the control group, usual clinical practice will be followed from the third trimester of pregnancy to promote BF. In the intervention group, and in addition to usual clinical practice, the women will use a free mobile application (LactApp^®^) from the third trimester to 6 months postpartum. The type of BF at birth, at 15 days and at 3 and 6 months postpartum and the causes of cessation of BF in both groups will be monitored. The hypothesis will be tested using inferential analysis, considering an alpha of 5%. The study protocol was approved by the Clinical Research Ethics Committee of Hospital de la Ribera (Alzira, Valencia, Spain) in February 2021. A per protocol analysis and an intention-to-treat analysis will be performed. Discussion: This study will identify the influence of a mobile application on improving BF rates. If the application proves effective, we will have a tool with free information available to any user at any time of day, which may be complemented by normal clinical practice and be integrated into our health care system. Trial registration: ClinicalTrials.gov ID: NCT05432700.

## 1. Introduction

The World Health Organization (WHO) recommends exclusive breastfeeding (EBF) for the first six months of an infant’s life, followed by complementary feeding until the infant is two or more years old [1]. The WHO firmly supports this type of feeding due to the clear benefits of breastfeeding (BF) for both the infant and the mother [2,3,4].

In Spain, the EBF rates at 6 months fall well short of the international recommendations [5]. Different studies have found the BF rates to be about 70% at maternal discharge, 68.4% at 6 weeks of life, and 24.7% at 6 months postpartum [6], though other more local studies report even lower rates [7]. A recent study on the prevalence of EBF up to 6 months of age carried out in our setting [8], involving a selected sample of women with an early start of BF in 87.7% of the cases, documented an EBF rate of 38.6% at 6 months postpartum, which is far below the worldwide target of 50% EBF at 6 months established by the WHO for the year 2025 [1].

A great variety of beneficial methods for promoting BF have been evaluated [9]. A number of health interventions have shown improvement of the BF rates, with proactive measures and the earliest intervention possible being the most successful strategies [10]. Both individualized and personalized support, as well as telephone mediated supportive measures, have demonstrated favorable outcomes [11,12], and the combination of various of these interventions enhances the effects and outcomes [13,14].

At present there are new interventions that still need to be tested for their long-term efficacy, such as the use of mobile applications [15,16]. In this context, mobile health services, mHealth, are defined as medical and public health practices compatible with mobile devices such as smartphones, patient monitoring devices, personal digital assistants and other wireless devices [17,18]. A large proportion of the European population consults online information for its health problems [19]. These users consider that the information they find is going to be useful for them [20]. On the other hand, healthcare systems increasingly make use of online services in support of users and healthcare professionals, including the utilization of mobile applications [21]. Nevertheless, it must be taken into account that the use of such tools is not proportional within the population, and that we must ensure that the information provided is not only based on the best available scientific evidence, but is also accessible to women at risk of social exclusion [22]. In line with different studies, the application of a protocolized intervention that is accessible and adapted to the needs of women effectively improves the rates and duration of BF [4,13,14,23,24,25,26].

On the other hand, while there is no single definition of health literacy (HL), the term refers to user knowledge and skills in adequate decision making in sociosanitary care [27]. Such skills include reading, writing, making calculations, communication capacity and—increasingly so—the use of information technologies. Deficient HL has been related to poor health outcomes, including the early suspension of BF [28,29,30], which is one of the most relevant public health problems and is of special importance in the maternal–childhood population.

In Spain, few randomized clinical trials have analyzed the benefits of interventions based on mobile devices in BF. The main objective of this study is to determine the influence of an intervention program in maintaining BF up to 6 months postpartum. The secondary aim is to assess the HL level of the participants and its association to the early (less than 6 months postpartum) suspension of BF.

## 2. Materials and Methods

### 2.1. Study Design

A multicenter, randomized controlled trial (RCT) of parallel groups has been designed. The clinical trial will be described according to the Consolidated Standards of Reporting Trials (CONSORT) [31] and using the Template for Intervention Description and Replication checklist (TIDieR) [32]. The study has been registered on ClinicalTrials.gov Identifier: NCT05432700.

### 2.2. Recruitment

The study will be conducted in three public hospitals in eastern Spain (Hospital Lluis Alcanyis, Hospital General de Castellón, and Hospital Universitario de la Ribera), and in one hospital in the western part of the country (Hospital San Pedro de Alcántara de Cáceres). The four hospitals serve a total population of 500,000 inhabitants, with an average of 5000 births a year. The women will be included during the third trimester of pregnancy in the different primary care midwife consulting rooms of each of the participating centers.

The study exclusion criteria are: females under 16 years of age; women with cognitive impairments, language barriers, or illiteracy (not able to read Spanish); non-availability of a mobile device with internet connection; newborn infants with congenital malformations; twin or multiple pregnancies; and admission to the Neonatal Intensive Care Unit (NICU), prenatal death or stillbirth, or postpartum complications requiring admission of the mother to the intensive care unit (ICU). Women failing to respond to the automated messages from the platform after three attempts will also be excluded, in the same way as those women in the control group who have used the LactApp^®^ application on their own initiative. Figure 1 shows the monitoring to be carried out during the study.

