#### 2.5.3. Intervention Group (Mobile Application Group)

From the first recording during the first trimester, the women will be able to consult all the available information in the application. LactApp^®^ is a free access mobile application developed through Apple Store and Google Play, and can be consulted in English and Spanish [38,39]. The central function of LactApp^®^ is its automated nursing consultation structure. This tool also uses artificial intelligence and is available 24 h a day with a connection to the Internet, providing convenient and personalized support. LactApp^®^ includes a self-management form based on over 50 decision trees with questions and answers developed by nursing experts, and is supported by scientific evidence and current official health recommendations. The questionnaire generates over 2300 personalized replies that can be reached through over 76,100 potential routes that vary fitting to the profile of the users and the options selected by the latter. In addition, the application reminds the user about the following issues, depending on the entered date of birth:The first four weeks: positioning of the infant for breastfeeding, frequency of milk intake, number and consistency of stools, general care of the breast, and weight gain of the newborn. For women providing food supplements, the tool offers counseling and support for returning to breastfeeding.From months two to three: recommendations on milk extraction to create a reserve in case of having to return to work or leave home, with instructions on handling and storage of the collected milk.From months four to six: how to use the milk reserve (if any) and techniques for administering the stored milk, placing emphasis on the importance of supporting BF and the advisability of not using other types of feeding.

If the intervention is effective and differences are found between the two groups, an analysis will be conducted within the intervention group to analyze the profile of women who are less likely to abandon BF at 6 months based on baseline variables, by adjusting a multiple logistic regression model, estimating the corresponding ORs and 95%CIs.

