### 2.7. Baseline Variables

The following variables will be collected at baseline:

- Sociodemographic variables: maternal age at the probable date of delivery, country of origin (Spain/foreign), level of education (primary school or lower/secondary school/university), employment status (self-employment/professional/managerial employment/employee/unemployed/student/not looking for a job), civil status (single/married/separated-divorced), partner (yes/no), number of live offspring, previous experience with breastfeeding (yes/no), participation in maternal education groups (yes/no), reception of previous information on BF (yes/no), and participation in BF support groups (yes/no).

- Variables related to health literacy: as a screening tool, use will be made of the HLS-EU-Q16, which evaluates the HL of the population based on 16 items scored by means of a Likert scale from “very easy” to “very difficult”. This is a unifactorial scale with good internal consistency as measured by McDonald’s omega, with a value of 0.982 in the Spanish population [34].

- Variables referred to health-related quality of life: use will be made of the EQ-5D [40] in the baseline measurements and at 3 and 6 months. This scale is very sensitive to quality of life measures and has been shown to be even more sensitive in women [41]. It comprises 5 items related to mobility, personal care, daily activities, pain/discomfort, and anxiety/depression. It uses a visual analogue scale (VAS) from 0 to 100 for measuring health condition at the time of application of the questionnaire [42].

- Variables related to self-efficacy of BF: the measurement of self-efficacy will be made with the BSES-SF scale in its Spanish version [37]. This instrument consists of 14 items scored by means of a Likert scale from 1 (not at all) to 5 (always). The BSES-SF is a unidimensional scale with a Cronbach alpha of 0.79 in its Spanish version.

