### 2.8. Data Analysis

An analysis will be performed of the baseline characteristics between the group of possible losses to follow-up and the group of women that complete follow-up, based on two-input tables and the comparison of means, using the Fisher exact test or Mann–Whitney U-test, as applicable.

Testing of the homogeneity of groups will be completed regarding the baseline variables and birth-related parameters and the suspension of BF at 6 months, using two-input tables and the chi-square test (χ^2^) or Fisher exact test, as applicable, while the comparison of means will be performed using the Mann–Whitney U-test.

A per-protocol (PP) analysis and intention-to-treat (ITT) analysis will be carried out. In the PP analysis, continuous variables will be reported as the mean and standard deviation (SD), or as the median and interquartile range (IQR) in the case of a non-normal data distribution, while categorical variables will be reported as frequencies and percentages. Data normality will be assessed using the Kolmogorov–Smirnov test.

In the ITT analysis, sensitivity referring to losses during follow-up will be assessed, with the response variable of the intervention group being assigned the worst result possible (suspension of BF at 6 months) and the control group being assigned the best result possible (no suspension of BF). Evaluation of the differences in response variable between the two groups will be performed, with all randomized subjects, applying the chi-square test.

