## 4. Limitations

The present study has its limitations. The level of adherence or decisions of the pregnant women when the issue of breastfeeding is raised during the monitoring of pregnancy may depend on a number of factors such as the type of information given to the women and the way in which the health professionals communicate with them. In effect, we consider that favorable health outcomes to be largely dependent upon the complex interaction between the health professional and the patient or user. However, the aim of our study is to explore the patient-related factors that facilitate or complicate BF, such as poor health literacy, with reference to the body of literature cited in the protocol. Since there is currently no standardized and protocolized mechanism for determining the skills of pregnant women in making effective use of the information provided, we consider it prudent to assume that the information supplied will be more or less the same for each woman (LactApp^®^ + professional), and that women with limited HL will be more prone to making suboptimal decisions as a result. In view of these shortcomings, we feel that it will be difficult to find compensation mechanisms for these women. Logically, this does not obviate the individual efforts which the professionals may make to solve problems such as poor understanding or language issues. Nonetheless, we believe that the added complexity of trying to systematize and define such efforts falls beyond the scope of our study. Furthermore, a contamination effect could occur among the women participating in the study, relating to the exchange of information regarding the use of the mobile application. This could be detected through the periodic electronic nursing follow-up surveys, evaluating whether the women in the control group make use of online tools. Such use would be reason for exclusion from this study. Another limitation may be the number of losses over follow-up. The self-completed electronic survey via the Internet has many advantages such as speed of data collection, lower cost, and can provide an attractive design for the respondent [41]. The downside is that there may be a lower response rate, which may affect the results obtained. In order to control for such selection bias and break of randomization, an analysis will be performed of the characteristics of the group of dropouts, along with an intention-to-treat analysis.

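### No app-use criterion applies before allocation to both arms; the only LactApp rule excludes control-arm users after randomization

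*Protocol article*

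**What the plan says.** Section 2.2 of the protocol article lists the exclusion criteria. They cover age, cognition, language and literacy, and then "non-availability of a mobile device with internet connection; newborn infants with congenital malformations; twin or multiple pregnancies", followed by intensive-care admission of mother or infant and perinatal death. None of these concerns app use. A further sentence in the same section also excludes women who do not answer the platform's messages, and "those women in the control group who have used the LactApp^®^ application on their own initiative".

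Section 4 (Limitations) says how such use would be found: "This could be detected through the periodic electronic nursing follow-up surveys, evaluating whether the women in the control group make use of online tools". It also gives the consequence: "Such use would be reason for exclusion from this study".

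Section 2.5.3 says that LactApp "is a free access mobile application developed through Apple Store and Google Play". The baseline list in section 2.7 includes "previous experience with breastfeeding (yes/no), participation in maternal education groups (yes/no), reception of previous information on BF (yes/no", but no item that is clearly about LactApp use before entry. Under section 2.5.1 the initial survey is completed after the woman has received her envelope.

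Section 2.8 states: "A per-protocol (PP) analysis and intention-to-treat (ITT) analysis will be carried out". The intention-to-treat comparison is to include all randomized women.

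**The concern.** Anyone can install the intervention without the trial. Women enter in the third trimester, and those who have breastfed before are eligible, so some may already have the app when they are approached. This can be learned before allocation, when one rule can be applied to everyone without touching the randomization. The plan instead has a rule that needs the allocation to be known and covers only the control arm.

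Two things are at stake. Removing existing users from control while keeping their counterparts in the app arm makes the compared groups differ in a characteristic fixed before randomization. Keeping them in both arms shrinks the contrast, because some controls are not app-free and some women in the app arm gain less than the plan assumes.

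**Working it through.** **The plan's own figures.** Section 2.4 gives suspension of 60% versus 40%, significance level 0.05, power 85%, a balanced design, 333 women, and 399 after 20% losses. Two-sided testing is assumed.
- Per arm: [1.96·√(2·0.5·0.5) + 1.036·√(0.24 + 0.24)]² / 0.20² = 110.7, so 111, or 222 in total. The stated 333 is not reproduced. That is a separate matter, but it explains why power below starts well above 85%.
- Losses: 333 × 1.2 = 399.6, which matches 399 when truncated. With 20% lost, 399 × 0.8 = 319.2 women are evaluable, or 159.6 per arm.

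**Who the rule reaches.** Take a woman who already uses the app when she is enrolled.
- Before the envelope: no criterion applies to her.
- Allocated to control: she meets the exclusion in section 2.2, which is detected in follow-up surveys.
- Allocated to the app: no rule applies and she stays.

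**If she stays in both arms (intention to treat).** Let f be the share of existing users. It is not in the documents and is assumed here. Suppose users have the app-arm rate of 40% in either arm. Then control = (1 − f) × 60% + f × 40%, and the app arm = 40%. Power = Φ{[Δ − 1.96·√(2p̄(1 − p̄)/n)] / √[(p_c(1 − p_c) + p_a(1 − p_a))/n]} with n = 159.6 and p̄ the mean of the two rates:
- f = 0: 60% vs 40%, power 95.0%
- f = 5%: 59% vs 40%, power 92.8%
- f = 10%: 58% vs 40%; (0.18 − 1.96 × 0.05596) / 0.05505 = 1.277, power 89.9%
- f = 20%: 56% vs 40%, power 81.9%

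Section 2.8.2 gives a significance level of 0.005, in conflict with section 2.4. At that level the same calculation gives about 78%, 66% and 52% for f = 0, 10% and 20%.

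**If she is removed from control only (per protocol).** The loss of numbers matters little: at 333 evaluable women and f = 10%, control falls from 166.5 to about 150 and power from 95.8% to 94.8%. The problem is comparability. Suppose the app has no effect, non-users have 60% suspension, and self-selected users have a rate lower by d. Control without users is 60%, the app arm is 60% − f·d, and the false difference is f·d:
- f = 10%, d = 10 points: 1 point
- f = 20%, d = 20 points: 4 points
- f = 30%, d = 20 points: 6 points

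Both f and d are assumptions. If users were instead women more likely to stop, the sign would reverse.

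**If removed controls are treated as losses.** Section 2.8 assigns lost controls the best outcome. It does not say whether excluded app users count as lost. If they did, at f = 10% control would be 0.9 × 60% = 54%, against 58% when their own outcomes are used.

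**The case against.** The strongest reply is that the protocol does address app use. The control-arm exclusion carries no start date, so it can cover use before allocation. A reader who overlooks it might infer that existing users are simply carried in both arms and contribute no contrast. The documents do not support that: control users are to be excluded, so the dilution figures apply only where all randomized women are analysed. This part of the reply stands. It does not remove the problem, because the exclusion is one-sided and comes after allocation.

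A reader might also infer that any past user already has the whole intervention. That goes too far. Section 2.5.3 describes reminders keyed to the entered date of birth, through month six. A woman who opened the app earlier in this pregnancy has had none of these for this infant, and one who used it with an earlier child may not be using it now. Giving every existing user the 40% rate therefore probably overstates the dilution.

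Third, section 2.7 lists use of digital tools, with the tool to be named. It sits under education received over six months, so its timing is unclear. Nothing ties it to eligibility, and the initial survey follows the envelope in any case.

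Finally, this is a condensed article without an inclusion list, and its flowchart is not shown, so a fuller eligibility list may exist. But the point does not rest on silence alone: the article states an app-use rule and ties it to one arm.

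**Conclusion.** The point holds as a defect in where and to whom the app-use rule applies. Existing users can be randomized and are then treated differently by arm, which opens the per-protocol comparison to selection bias. In the analysis of all randomized women they weaken the contrast instead.

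The size is not known, because the documents give neither the share of existing users nor their suspension rate. Under the stated assumptions, a 10% share costs about 5 points of power at two-sided 5% (95% to 90%), and power drops below the planned 85% only at the assumed 20% share (82%). It would be wrong to conclude that the trial is underpowered for this reason at the 0.05 level. The false difference of 1 to 6 points in the one-sided removal illustrates a mechanism and is not an estimate.

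**What to change.** In section 2.2, add an exclusion criterion for current or previous use of LactApp. The midwife assesses it for every woman before the envelope is given and applies it regardless of arm. Ask about LactApp within a list of several apps so that it is not singled out. Women then enter both arms without prior use of the app, and the control-arm rule is no longer needed for use that predates allocation.

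The cost is one screening question and one protocol line. A few interested women become ineligible, among them some experienced mothers, which slightly narrows applicability. The question also names the app to some women later allocated to control; the list of several apps reduces this but does not remove it. Recording prior use before allocation and stratifying on it would also treat the arms alike, but it would leave existing users, and so the dilution, in the trial.

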### 2.3. Randomization and Blinding

The women will be included during the third trimester of pregnancy in the different primary care midwife consulting rooms of each of the participating centers. After reading the information sheet and giving informed consent, the women will be registered on a webpage created for the purpose of the research and will be assigned to one of the groups (control or intervention) via a simple randomization process, until the estimated sample size has been reached. Randomization will be performed using Epidat v.4.2. [33], with groups of equal size.

Allocation concealment will be carried out, with blinding of the midwives in charge of recruiting the women, providing them with sealed, opaque and sequentially numbered envelopes to be delivered to each new participant wishing the participate in the study.

The research team will prepare the envelopes based on the random allocation sequence. Each envelope will contain a card with a QR code providing access to the study follow-up platform. Follow-up data collection will be conducted by another researcher blinded to the group status of participants. Only the data manager will have access to all of the integrated data (the data reported by the participating women through the surveys and the birth/postpartum data reported by the principal investigators).

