### 2.5. Intervention

#### 2.5.1. Both Groups

The study sample will be compiled during the third trimester of pregnancy in the different primary care midwife consulting rooms of each of the participating centers. After receiving the envelope, the women will read the QR code with their mobile device and will be registered in the nursing platform created for the study, after accepting the privacy policy statement. Both the intervention group and the control group will undergo an initial survey to record sociodemographic data, previous experience with BF, and the probable date of delivery. In addition, two self-administered questionnaires will be completed—one on HL (HLS-EU-Q16) [34] and another on health-related quality of life (EQ-5D-5L) [35]—through the e-mail account registered on the platform.

Planning of reminders via e-mail will be performed to obtain information referred to follow-up, at all times avoiding the provision of any extra information on BF. During pregnancy, based on the pregnancy protocol and usual clinical practice, parent role education and nursing workshops will be planned for both groups, with the availability of different manuals to be given to each pregnant woman [36].

The platform will send serial e-mails to both study arms (intervention and control) for follow-up on the type of nursing after birth, at 15 days, at 6 weeks, and at 3 and 6 months. Questions will be asked regarding the type of nursing and BF-related problems, and the breastfeeding self-efficacy scale—short form (BSES-SF) will be applied [37]. In the event of the suspension of BF, the reason for suspension will be recorded, along with the total breastfeeding time. At 3 and 6 months postpartum, new measurements will be made with the health-related quality of life questionnaire (EQ-5D).

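### Non-response to the platform's messages is a post-randomization exclusion in section 2.2, and the article does not reconcile it with the analysis of all randomized women in section 2.8

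*Protocol article*

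**What the plan says.** Section 2.2 (Recruitment) adds to the exclusion criteria: "Women failing to respond to the automated messages from the platform after three attempts will also be excluded". It puts these women on the same footing as control women who use the app on their own initiative. Section 4 (Limitations) says of that app use: "Such use would be reason for exclusion from this study".

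The order of events is given in two places. Section 2.3: "The research team will prepare the envelopes based on the random allocation sequence". Section 2.5.1: "After receiving the envelope, the women will read the QR code with their mobile device and will be registered in the nursing platform". The same section describes what the messages are for: "The platform will send serial e-mails to both study arms (intervention and control) for follow-up on the type of nursing after birth", with further rounds up to 6 months.

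Section 2.8 plans a per-protocol (PP) and an ITT analysis. In the ITT analysis, losses are set to suspension in the intervention arm and to no suspension in the control arm. The section continues: "Evaluation of the differences in response variable between the two groups will be performed, with all randomized subjects". Section 2.8.1 does not name the set used for the primary analysis.

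Section 2.7 defines the response variable as feeding status at 6 months: suspended if the infant is on supplementary feeding, not suspended if on breast or mixed feeding. On the electronic survey, section 4 concedes: "The downside is that there may be a lower response rate, which may affect the results obtained".

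**The concern.** A woman who stops answering is excluded under section 2.2 and analysed under section 2.8. No sentence says which rule prevails. The exclusion is not limited to the PP set, and excluded non-responders are not said to be the losses that section 2.8 imputes. Two analysts could follow the text faithfully and build different ITT sets.

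There is also a data-collection problem. The rule does not say whether the three attempts refer to one survey, to all surveys together or to the last one. On some of these readings a woman can leave the trial before she is asked the single question that determines the primary endpoint. That outcome might have been obtainable, and it cannot be recovered at analysis.

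**Working it through.** **Step 1: timing.** The allocation is fixed when the envelopes are prepared (2.3). Registration on the platform follows receipt of the envelope (2.5.1), and platform messages follow registration. Every exclusion for non-response therefore removes a woman already randomized, on the basis of her response to the instrument that collects the outcome.

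**Step 2: what the label does to the result.** Inputs from section 2.4: suspension 60% (control) and 40% (app), 399 women (199.5 per arm), planned loss 20%. I take 399 as stated; whether it follows from its own inputs is a separate matter. Assumptions: 60% and 40% hold among responders, and the loss fraction L is equal in both arms. L = 5% and 10% are added to show the range.

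- Non-responders excluded: rates stay at 60% and 40%, with n = 199.5(1 − L) per arm.
- Non-responders imputed as in section 2.8: control = 0.60(1 − L); app = 0.40(1 − L) + L; n = 199.5 per arm.
- z = (control − app) / √[p(1 − p) × 2/n], where p is the pooled rate, here 0.50 throughout.

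| L | Excluded: control vs app | z | Imputed: control vs app | z |
|---|---|---|---|---|
| 5% | 60% vs 40% | 3.89 | 57% vs 43% | 2.80 |
| 10% | 60% vs 40% | 3.79 | 54% vs 46% | 1.60 |
| 20% | 60% vs 40% | 3.57 | 48% vs 52% | −0.80 |

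The imputed difference is 0.20 − 1.20L. With a standard error of √(0.25 × 2/199.5) = 0.0501, it falls below z = 1.96 once L exceeds (0.20 − 0.0981)/1.20 = 8.5%. It reaches zero at L = 0.20/1.20 = 16.7%, which is below the planned 20%.

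**Step 3: can the rule lose an obtainable endpoint?** The endpoint is a status at 6 months (2.7) and needs no answer at birth, 15 days, 6 weeks or 3 months. The women affected are those who use up three attempts earlier but would have answered at 6 months. The documents give no figure for this group, so I put no number on it. It could be small.

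**Step 4: direction of bias if non-responders are simply dropped.** All non-response splits here are assumptions. Suppose there is no true effect (60% in both arms) and control non-response is 20%, unrelated to outcome. Let a and b be app-arm non-response among women who stopped and who continued. Observed app-arm suspension = 0.6(1 − a) / [0.6(1 − a) + 0.4(1 − b)].

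- a = 30%, b = 10%: 0.42/0.78 = 53.8% against 60.0%. The chance of a significant two-sided result at 5% is about 20%.
- a = 25%, b = 12.5%: 56.3% against 60.0%, about 10%.
- a = 30%, b = 5%: 52.5% against 60.0%, about 27%.
- Reversed, a = 10%, b = 30%: 0.54/0.82 = 65.9% against 60.0%, so the bias runs against the app.
- The same a and b in both arms: no bias under no effect. Under a true 60% vs 40%, the 20.0-point difference becomes 19.9 points (25%/12.5%) or 19.6 points (30%/5%).

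Now apply the section 2.8 imputation to the first scenario. App arm: 0.42 + 0.22 missing = 64%. Control: 0.60 × 0.80 = 48%. The difference is 16 points against the app, z = 0.16 / √(0.56 × 0.44 × 2/199.5) = 3.2.

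**The case against.** The strongest defence is that non-responders are PP exclusions and ITT losses. Section 2.4 budgets 20% loss, section 2.6 promises to detail losses and their causes, section 2.8 compares losses with completers, and section 4 offers the dropout comparison and the ITT analysis as the answer to selection bias. This reading is coherent and may be what was meant. It is not written, however, and the parallel treatment of control app users, whom section 4 excludes from the study, points the other way. Nor is this detail left out by a condensed article: the exclusion rule is stated, and it conflicts with another stated rule.

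Two stronger readings are tempting and are not supported.

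- **That the rule makes the app look better.** A reader might infer this from step 4. Those figures describe a complete-case analysis only. They need response to depend on outcome differently by arm, which no section states; both arms receive the same e-mails. They also count all non-response, whereas women who never answer at 6 months are missing with or without the rule. The worst-case imputation of section 2.8 pushes the other way.
- **That a woman who ignores the 15-day or 6-week survey is removed.** The text does not say this. It does not specify which messages the three attempts refer to, and no section says that e-mails stop or that a 6-month answer already received is discarded. What stands is that the wording permits it and nothing rules it out.

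**Conclusion.** The point holds as an unresolved conflict between sections 2.2 and 2.8, together with an avoidable risk of losing 6-month outcomes. It does not establish a bias in favour of the app. The conflict matters because the label alone can move the planned comparison from a clear difference (60% vs 40%) to a non-significant one at 10% loss (54% vs 46%) and to a reversed one at 20% (48% vs 52%). These figures rest on the rates and sample size in section 2.4 and on equal losses in the two arms. The conflict itself needs no assumption about how non-response arises. The number of outcomes that the rule would needlessly lose cannot be estimated from the document.

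**What to change.** In section 2.2, either remove non-response from the exclusion criteria or state that it affects PP membership only. In sections 2.2 and 2.8, state that:

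- every randomized woman stays in the ITT set;
- later surveys, including the 6-month feeding question, continue to be sent after missed messages;
- a 6-month answer is used whenever it is given;
- only women whose 6-month status remains unknown count as losses for the imputation.

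The cost is a few sentences and a platform setting that keeps the e-mails running. The downside is some further automated messages to women who have not replied. Continued sending has to be in place during follow-up, because an outcome that was never requested cannot be restored at analysis.
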